### Screening and self-administered questionnaire

Participants' parents will complete a QR code online application form soliciting sociodemographic information [age, gender, educational background, monthly family household income, living circumstances, school year, participant's psychiatric history, and duration of ADHD diagnosis (in years/months)], age of diagnosis, duration of taking prescribed medications (in years/months), current drugs and dosages, and family history of psychiatric disorder.

Eligible subjects will then fill in the screening tool (The Swanson, Nolan, and Pelham Rating Scale (SNAP IV), and those with a SNAP IV mean score of >2 will be recruited. Subjects' medical history, treatment regime, and developmental history will be obtained by direct inquiry with subjects' parents either by Zoom interview or Facetime before neuroimaging and TPS treatment. Both participants and parents will be interviewed by the PI and the research personnel. Parents need to hold a valid medical certificate of his/her child's ADHD diagnosis and a prescribed formulation sheet during the online interview. Any parent who fails to show this proof will not be invited to participate in the trial.

### Randomization, allocation, and masking

All consenting participants will be listed in alphabetical order according to their surnames, and each participant will be assigned a unique identifier. An independent statistician ([name]) will use a computer-generated list of random numbers (www.random.org) to ensure the concealment of randomization. Randomization will be conducted by an independent statistician off-site using a stochastic minimization program to balance the gender, age, and SNAP-IV scores of the participants. Block randomization with blocks of 10 (total: 3 blocks) will be used to allocate treatment groups. Participants from each block will be randomly assigned to the verum TPS groups or the sham TPS groups on a 1:1 ratio. To avoid information flow, participants/parents and research associates will be blinded to the group allocation to minimize potential contamination of the effects of TPS or subject bias. The interventionist will not be involved in data collection or pre- and post-TPS measurements. Outcome measurements will be conducted by a research associate who is not involved in the group allocation. Participants and their parents will be asked to guess the grouping (verum TPS vs. sham TPS) in the last TPS session to determine the probability of guessing the group allocation correctly in the subject blinding (44).

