### Sample size

To the best of our knowledge, there is no interventional study evaluating the efficacy of TPS on ADHD. Based on our previous open-label pilot RCT (39) evaluating TPS in adults with major depressive disorder that showed a large effect size (d = 0.91), we hypothesize a large effect of TPS in this study. We used G^*^power version 3.1.9.4 to calculate the target sample size. With a statistical power of 95% and a statistical significance level of 0.05 to detect a medium between-groups effect size (d) of 0.91 with four measurement time points, each group will require 15 subjects. A total sample of 30 is required in this trial. The attrition rate in our pilot MDD trial was 0%. We expect that the attrition rate in this ADHD trial would be < 5%. Subjects dropping out of the 2-week intervention period will be replaced by another enrolled subject in this pilot study.

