## Trial status

This trial was registered with clinicaltrails.gov on 10 August 2022 (protocol version). Recruitment commenced from 1 June 2022 to 30 Sept 2022.

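### The plan names both stochastic minimisation and fixed blocks of 10 as the allocation method, without saying how they combine or how replacements for dropouts are allocated

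*Protocol article*

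**What the plan says.** All statements on the method stand in the protocol article, section Randomization, allocation, and masking, in this order:

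- Listing comes first: "All consenting participants will be listed in alphabetical order according to their surnames". Everyone on the list also receives an identifier.
- As the source of randomness, the plan says that the statistician, who is independent of the team, "will use a computer-generated list of random numbers (www.random.org) to ensure the concealment of randomization".
- A first allocation rule follows. The work is done away from the site, "using a stochastic minimization program to balance the gender, age, and SNAP-IV scores of the participants".
- The very next sentence gives a second rule: "Block randomization with blocks of 10 (total: 3 blocks) will be used to allocate treatment groups".
- Within a block, the split between verum and sham is random and equal, so 5 and 5.

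The same section names participants, parents and research associates as blinded. It keeps the interventionist out of data collection and outcome measurement, but does not list that person as blinded.

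Other sections bear on this. Sample size: "A total sample of 30 is required in this trial", with dropouts during the 2-week intervention replaced by another enrolled subject. Screening and self-administered questionnaire: "Both participants and parents will be interviewed by the PI and the research personnel". Interventions: the PI delivers the treatment. Sham TPS: the handpiece filling differs between arms. Subjects: recruitment spans 2 months. Trial status: "Recruitment commenced from 1 June 2022 to 30 Sept 2022".

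**The concern.** Two consecutive sentences give two different rules for the same act, and no sentence joins them. This is a conflict in the text, not a detail left to a fuller document.

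The choice of rule has three consequences. First, it decides whether the balance claimed on gender, age and SNAP-IV exists; SNAP-IV is the primary outcome, and with 15 per arm chance imbalance in its baseline is a practical matter. Second, it decides which factors the primary linear mixed model should carry. Statistical analyses provides for covariates only where sociodemographic factors differ significantly between groups, which is not how factors used in minimisation should be handled. Third, it decides how someone who enters late, such as a replacement, receives an allocation.

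The concealment statement adds to the difficulty. A random-number list generates a sequence; it does not hide it. Concealment comes from who holds the sequence and when each assignment is released. The off-site statistician supplies part of that; the list does not.

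**Working it through.** **1. Block arithmetic.** 3 blocks × 10 = 30, which reproduces the planned total; 1:1 within each block gives 5 and 5, so 15 per arm. The block sentence is consistent with the sample size. The difficulty is its neighbour.

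**2. The two rules side by side.**

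| Feature | Stochastic minimisation | Fixed blocks of 10 |
|---|---|---|
| Assignment depends on | Covariates of those already allocated, plus a random element | Places left in the block |
| Balance on gender, age, SNAP-IV | Sought by design | Left to chance |
| Exactly 5:5 in every ten | Not forced | Forced |
| Implied model factors | Gender, age, baseline SNAP-IV | None of these by virtue of allocation |

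The random-number list is not a third rival: it can supply the randomness for a block sequence. It conflicts only with minimisation, and only if it is used as a sequence made in advance.

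**3. Timing.** Listing all consenting participants before allocating suggests that the 30 are allocated together. A replacement for someone who drops out during the 2 weeks of treatment must enter later. It fits neither the list nor three complete blocks. At the expected attrition below 5%, this is fewer than 0.05 × 30 = 1.5 participants.

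**4. Predictability, if entry is sequential.** Assume pure blocks with a known size of 2k = 10 (k = 5) and an observer who knows all past arms.

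- Allocations certain in advance: 2k/(k + 1) = 10/6 = 1.67 per block, so 3 × 1.67 = 5.0 of 30 (16.7%).
- Expected correct guesses when always choosing the arm with more places left: k + (2^(2k)/C(2k, k) − 1)/2 = 5 + (1024/252 − 1)/2 = 6.53 of 10 (65.3%), about 19.6 of 30, against 50% by chance.

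Enumerating all 252 balanced sequences gives the same two values. If all 30 are consented and listed before allocation, both fall away for those 30.

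**5. Is minimisation less predictable?** I simulated N = 30 with three factors of two or three levels each, a one-third/two-thirds gender split, equal age and SNAP-IV bands, and 0.8 probability of the balancing arm. All these settings are assumptions; the plan gives none of them. An observer who knows covariates and past arms guesses about 74–75% correctly. One who tracks arm totals only guesses about 63–64%. Against 65% for blocks of 10, predictability gives no reason to prefer minimisation, although minimisation does remove the certain allocations at the end of a block.

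**The case against.** The strongest reply is that this is under-specification rather than contradiction. If covariates are known for a listed batch, a program could choose at random among 5:5 splits that also balance gender, age and SNAP-IV. That is possible, and it means blocks do not by logic exclude covariate balance. But the text does not describe such a procedure, and the ordinary meanings of the two terms do not yield it.

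A reader might infer more: that the PI, who interviews candidates and handles the sham handpiece, can deduce upcoming allocations and steer entry. The document does not support this as a plain statement.

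- That the PI knows the arm is a fair inference from the list of blinded roles and the differing handpiece filling, but it is not stated.
- Randomisation is by an independent statistician off-site, and the alphabetical list points to allocation after consent.
- Enrolling 30 adolescents over a 2-month or 4-month window and allocating afterwards is feasible.
- The scope for steering is limited: entry turns on documentary proof of diagnosis and on a parent-rated SNAP-IV threshold.

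What remains is that the text does not fix the timing. Foreknowledge is therefore possible if entry was sequential, and for replacements in any case. If a replacement simply takes the vacated place to keep 15:15, its arm is known beforehand to whoever treated the dropout.

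The last objection is that recruitment may be over, so the scheme can no longer be changed. That is fair, and it alters the form of the remedy but not the need for it.

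**Conclusion.** The point holds for the conflict between minimisation and fixed blocks of 10, and for the mismatch between the alphabetical list and the replacement of dropouts. Confidence in these is high because they rest on the wording alone. The count is two methods in conflict, not three.

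The predictability figures are correct as arithmetic, but they describe only one possible reading: sequential entry, pure blocks and known past arms. They do not show that allocation in this trial was predictable, and they do not rank the two schemes. Where the list is complete before allocation, foreknowledge for the initial 30 is nil.

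**What to change.** Keep one scheme and delete the other. If recruitment ended as Trial status dates it, state which scheme was actually run.

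- **If minimisation:** delete the blocks of 10, state the random element, and include gender, age and baseline SNAP-IV in the primary mixed model whether or not they differ at baseline.
- **If blocks:** delete the claim of balance on gender, age and SNAP-IV.
- **Either way:** state that the off-site statistician releases each allocation only after consent and eligibility are locked, and that this applies to replacements too. Say how a replacement's arm is determined. Remove the statement that the random-number list ensures concealment.

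The cost is wording and a little more analysis work. Under minimisation the arms may differ by about 2 participants.

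Neither scheme changes the PI's double role as interviewer and interventionist. Locking eligibility before release is what protects against it.

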### Interventions

TPS intervention will be performed at the Integrative Health Clinic, at the Hong Kong Polytechnic University. A licensed mental health practitioner (PI: [name]) will deliver the intervention.

### TPS procedures

The TPS system consists of a mobile single transducer and an infrared camera system for MR-based neuro-navigation (NEUROLITH, Storz Medical AG, Tägerwilen, Switzerland). TPS generates single ultrashort (3 μs) ultrasound pulses with typical energy levels of 0.2–0.25 mJ/mm^2^ and pulse frequencies of 4–5 Hz (pulses per second). During the TPS session, participants will be sitting in a comfortable electronic chair in the treatment venue. Participants will wear a BodyTrack system consisting of a 3D camera, tracking glasses with markers, and a TPS handpiece with markers (Figure 2). This BodyTrack system ensures that the participant's head matches with his/her fMRI T1 images previously taken in UBSN so that each TPS pulse applied can be visualized and documented in real-time. Real-time tracking of the handpiece position enables automatic visualization of the treated brain region. The energy applied will be highlighted in green (Figure 3). The interventionist will use the variable stand-offs at the handpiece for depth regulation and manual movement of the handpiece over the skull with real-time visualization of participants' fMRI brain images. The whole treatment session will be recorded for *post-hoc* evaluation of the individual intracerebral pulse localizations (Figure 4).

**Figure 2 F2:**
[figure not shown]
Transcranial pulse stimulation (TPS) system.

**Figure 3 F3:**
[figure not shown]
Transcranial pulse stimulation (TPS) (STORZ MEDICAL) post-intervention images.

**Figure 4 F4:**
[figure not shown]
Transcranial pulse stimulation system and TPS treatment venue in IHC/PolyU.

### TPS Intervention dose

In this proposed study, we will deliver 800 pulses to the subject's left DLPFC in each session (total: 4,800 pulses). All participants (in both active and sham TPS groups) will receive six 30-min TPS sessions over 2 weeks (i.e., 3 sessions/week, on alternate days, total treatment time: 3 h) using energy levels of 0.25 mJ/mm^2^ and a frequency of 4 Hz. We believe that a 2-week TPS intervention will be sufficient enough to test the efficacy of TPS on ADHD (29, 39). Participants will be followed up immediately after stimulation at 2 weeks, 1 month, and 12 weeks (Figure 1). We believe that a post-treatment follow-up of up to 3 months is sufficient to evaluate the sustainability of TPS on ADHD (29, 39).

### Sham TPS

Participants will be given an identical TPS intervention dose, but the silicone oil used in the verum TPS group will be replaced by an air-filled cushion in the handpiece. Participants will also hear sounds and stimuli similar to the verum TPS group.

### Fidelity

To ensure the fidelity of the intervention, the project team will ascertain whether the interventions will be delivered as intended. The interventionist (PI) obtained a Ph.D. in social sciences (HKU) and is a UK- and HK-licensed mental health professional with more than 10 years of clinical experience in mental health and neuroscience. The research associate will issue WhatsApp message reminders (e.g., TPS intervention schedule, fMRI scan appointments, and f/u appointment slips) to parents and will report subjects' progress, and indicate adverse effects and adherence throughout the trial period.

### Safety, adverse effects, and risk indicators of TPS

TPS uses very low energy for brain stimulation, thus TPS intervention should not cause any serious adverse effects such as intracranial bleeding, edema, or other intracranial pathology, as confirmed in previous studies (29, 39). Although this TPS system has obtained clinical certification (CE) indicating that it is a safe intervention, we will prepare a checklist stating all the potential adverse effects associated with TPS administration (29) and monitor the subject's tolerability and adverse events in each session throughout the trial period. In the pilot RCT on MDD (39), a few subjects reported transient headaches (< 2 h) (4%) but none required pain analgesics. Nonetheless, all subjects will be covered by master trial insurance in this study.

### Ethical and data security considerations

Participants' data in both groups will be stored in two separate datasets with an identifier linking these data. Both sets of data will be encrypted using TrueCrypt (http://www.truecrypt.org). The data from the baseline and 12-week follow-up will be linked according to personal data. All precautions in data protection will be taken, as suggested by TrueCrypt. To prevent leakage of personal data, only the PI will have access to the personal dataset. Written consent will be obtained from all participants and both parents. An information sheet containing the purpose of this trial and the potential risks and benefits of its procedures for undertaking MRI scans in UBSN/PolyU and TPS will be provided to all parents. Participants' parents will be informed of their children's anonymity; withdrawal or non-compliance will not result in any consequences.

## Outcome evaluation (primary and secondary outcomes)

### Baseline assessment

#### Demographic data

The subjects' basic demographic data, including age, gender, body mass index, years of education, birth history, number of siblings, monthly household income, and first-degree family members' history of ADHD (yes/no), will be collected upon study entry. Details of the subjects' psychiatric history, including the age of diagnosis and any developmental delays or serious injury on any bodily parts, or serious physical illness(es), will also be recorded at the baseline assessment.

### Primary outcome

#### Attention deficit, hyperactivity impulse, and oppositional defiance

The Swanson, Nolan, and Pelham Rating Scale (SNAP IV) will be used to measure participants' attention deficit, hyperactivity impulse, and oppositional defiance. SNAP IV consists of 26 items summarized into three factors: attention deficit, hyperactivity impulse, and oppositional defiance. Parents, based on their general impressions of their children, rate the severity of symptoms on a Likert scale (0–3). A mean score of <1 indicates “normal” or “remission”; a mean score of 1 is defined as the demarcation between attention deficit and hyperactivity-impulsivity; a mean score of >2 indicates “abnormal.” SNAP-IV is a reliable and valid scale used in RCTs (45) and has good psychometric properties that can be used for the Chinese population (46).

### Secondary outcomes

#### Clinical Global Impression

The Clinical Global Impression (CGI)—severity and improvement scale (CGI-S and CGI-I) is generally used to assess illness severity and global improvement. CGI-S is a 7-point clinician rating scale based on observed and reported symptoms, behavior, and function in the past 7 days. CGI-I is a 7-point scale to assess whether the patient's ADHD condition has improved or worsened compared to the baseline. CGI-S and CGI-I will be used to supplement each other (47). These scales had been used in a double-blinded placebo-controlled RCT (48).

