**Methods:**

This study proposes a double-blinded, randomized, sham-controlled trial including TPS as an intervention group and a sham TPS group. Both groups will be measured at baseline (T1), immediately after the intervention (T2), and at the 1-month (T3) and 3-month follow-ups (T4).

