### Statistical analyses

All statistical analyses will be performed using the statistical software R for Windows (R version 4.1.0). Means and standard deviations (SD) for the continuous variables will be presented, while numbers and percentages for the categorical variables will be shown. A *p*-value of < 0.05 is considered statistically significant. Sociodemographic differences between the TPS group and the sham TPS group will be analyzed using the Chi-square test and *t*-test. If there are significant differences between sociodemographic factors, covariates will be considered confounding variables in the analyses. The normality of the primary outcome (SNAP-IV) scores will be tested by the Shapiro–Wilk test for each combination of factor levels (group and time). *T*-test will be used to test the baseline difference. A linear mixed model will be used to test the group (between-subject factor), time (within-subject factor), and group × time interaction effects of the SNAP-IV score between the TPS group and the sham TPS group. *Post-hoc* comparisons between groups and time points will be conducted using a *t*-test with Bonferroni correction. The normality of the secondary outcome scores will be tested by the Shapiro–Wilk test for each time point. For normally distributed outcomes, a linear mixed model will be used to determine whether the outcome scores are significantly different between the pre- and post-tests. For outcome scores that deviate grossly from normality, a non-parametric Friedman test will be used to test the mean difference. A Cohen's *d* effect size for each outcome will be calculated, where *d* = 0.2, 0.5, and 0.8 correspond to small, medium, and large effect sizes (54). Missing data will be managed by multiple imputations (55). For the neurological rs-fMRI data, a longitudinal voxel-based morphometry (VBM) will be used to examine whether TPS produces local changes in gray matter. Specifically, relative local increases and decreases between pre- and post-intervention scans will be compared within and between study groups. The diffusion MR data will be analyzed using the diffusion tensor model (56). Two standard diffusion indices will then be obtained: the apparent diffusion coefficient and the fractional anisotropy. Pre- and post-treatment DTI scans will permit the assessment of changes in axial diffusivity, with lower values being interpreted as the structural enhancement of white matter.

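### CGI-I is a change-from-baseline rating with no pre-treatment value, so the pre/post rule set for secondary outcomes cannot be applied to it

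*Protocol article*

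**What the plan says.** Under Clinical Global Impression, the protocol article names two 7-point scales as secondary outcomes. The first rates current severity: "CGI-S is a 7-point clinician rating scale based on observed and reported symptoms, behavior, and function in the past 7 days". The second rates change: "CGI-I is a 7-point scale to assess whether the patient's ADHD condition has improved or worsened compared to the baseline". Both are kept, since "CGI-S and CGI-I will be used to supplement each other".

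The Methods paragraph of the abstract gives the schedule: "Both groups will be measured at baseline (T1), immediately after the intervention (T2), and at the 1-month (T3) and 3-month follow-ups (T4").

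The Statistical analyses section sets one procedure for the secondary outcome scores. Normality is checked by Shapiro–Wilk at each time point. For normal outcomes, "a linear mixed model will be used to determine whether the outcome scores are significantly different between the pre- and post-tests". For grossly non-normal outcomes, "a non-parametric Friedman test will be used to test the mean difference". CGI-I is not treated separately.

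On who measures, the Randomization, allocation, and masking section says: "Outcome measurements will be conducted by a research associate who is not involved in the group allocation". It also says: "The interventionist will not be involved in data collection or pre- and post-TPS measurements".

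**The concern.** A rule that contrasts scores before and after treatment needs a score before treatment. CGI-I has none, because each rating already expresses the difference from baseline. Whoever analyses the trial will have to depart from the stated rule for this outcome, and the choice would then be made with data in hand. The obvious fallback, running the same tests on the visits that do exist, answers a question the trial does not ask.

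The CGI has some weight here. SNAP-IV and the ADHD RS-IV are both described as rated by parents. The CGI is the only symptom measure not so described, which makes it a useful cross-check on the parent-rated primary outcome. It is still one secondary outcome among several, and the Hypotheses section does not name it.

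**Working it through.** The plan gives no figure to reproduce on this point. The check counts the scores that can exist and sets them against what each stated test needs.

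**Inputs**
- Visits: T1 (before treatment), T2, T3 and T4 (after treatment), from the abstract. That is 1 pre and 3 post.
- Subjects: 30, from the Sample size section.
- CGI-S: severity over the past 7 days, so it can be rated at any visit.
- CGI-I: change relative to baseline, so it can be rated only after baseline.

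**Scores available with complete follow-up**

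| Scale | Pre, per subject | Post, per subject | Trial total |
|---|---|---|---|
| CGI-S | 1 of 1 | 3 of 3 | 30 × 4 = 120 |
| CGI-I | 0 of 1 | 3 of 3 | 30 × 3 = 90 |

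**Each stated step applied to CGI-I**
1. *Shapiro–Wilk at each time point.* T1 has no values, so the check cannot be done there.
2. *Linear mixed model, pre versus post.* The T1 level is empty in both arms, so the contrast cannot be estimated. The plan's multiple imputation does not help: with 0 of 30 T1 values observed, there is nothing to base an imputation on, and the value is undefined rather than missing.
3. *Friedman test.* It can be run on T2, T3 and T4. It then asks whether ratings differ among three post-treatment visits within subjects. It makes no pre/post comparison and has no term for treatment arm.

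**A generous reading.** Suppose the secondary model is meant to carry the group, time and group × time terms that the article lists for SNAP-IV. With CGI-I limited to T2–T4, the interaction asks whether the difference between arms varies across follow-up. A benefit that is equal at all three visits would leave the interaction at zero. Because CGI-I is already a change score, the treatment effect is the difference between arms at each visit. The stated rule does not call for that comparison.

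**The same steps applied to CGI-S.** All four visits have values, so the normality check, the pre/post model and the Friedman test can all be computed as written.

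**The case against.** The strongest reply is that this is a narrow misfit in a condensed article, and that the arm comparison by visit could sit in an analysis plan that is not shown. That would be decisive if the article were silent. It is not: it fixes a rule for the secondary outcome scores, and that rule cannot be carried out for one of the outcomes it names. What stands of the reply is the scale of the point: one subscale, one sentence, a secondary outcome.

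Three stronger readings are tempting, and the article does not support them.

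- *The CGI as a whole cannot be obtained or tested.* CGI-S has a baseline value and fits the rule, and CGI-I can be collected at T2–T4.
- *No rater is both a clinician and blinded.* A reader might infer this because the only person described as a licensed mental health practitioner is the interventionist, who is barred from measurement and not listed among those blinded. But the section on masking lists research associates as blinded and assigns outcome measurement to one. The associate's qualification is not stated, an article commonly leaves it to the full protocol, and nothing says this person is not a clinician. Nor does the Sham TPS section say who exchanges the oil for the air cushion, so that cannot be used to show that the interventionist knows the arm.
- *The test would produce a false positive.* If T1 were filled with a constant no-change score of 4, a mean improvement of 0.5 to 1 point with SD 1 in all 30 subjects would give t = 0.5/(1/√30) = 2.74 to t = 1/(1/√30) = 5.48, with no difference between arms. The arithmetic is right, but the filled-in T1 score, the shift and the SD are all assumed, and no part of the article calls for such an entry. A pooled pre/post test picks up sham response on any outcome, so these figures do not measure the CGI-I problem.

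**Conclusion.** The point holds for CGI-I only. Its definition rules out a T1 value, and the rule set for the secondary outcome scores requires one. As written, the pre/post test cannot be performed on CGI-I. Restricted to the 90 possible post-treatment scores, the Friedman version compares visits with each other and never verum with sham. This follows from the article's own definitions and schedule and needs no numerical assumption.

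The effect on the trial is limited: the SNAP-IV analysis, CGI-S and the other secondary outcomes are not affected by this defect. No size of bias is claimed. Who rates the CGI is a question for the sponsor to answer, not a shown inconsistency.

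**What to change.** In the Statistical analyses section:
- Exempt CGI-I from the pre/post rule and state that it is recorded at T2, T3 and T4 only.
- Compare verum with sham directly at those visits, for example by a mixed or ordinal model with group, visit and group × visit and with T1 CGI-S as a covariate. Report the difference between arms at each visit. With 15 per arm and seven categories (15/7, about two subjects per category on average), an ordinal model may be sparse, so a simpler fallback should be named in advance.
- Keep baseline-to-follow-up modelling for CGI-S.

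Separately, ask the sponsor to confirm that the blinded research associate who conducts outcome measurements is qualified to give the clinician rating that the CGI section describes. The scale does not need relabelling unless the answer is no.

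The cost is a few sentences in the protocol and the analysis plan. No visit, subject or instrument is added.
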